### Study setting and population

The study setting is the comprehensive ICU, Fuxing Hospital, Capital Medical University, Beijing, China. All patients admitted to our ICU with acute respiratory failure requiring mechanical ventilation and tracheotomy to assist weaning are screened daily for study eligibility.

Inclusion criteria are: (a) age ≥18-years-old; (b) Glasgow Coma Scale (GCS) score ≥10; (c) sedation with propofol, morphine, alfentanil and dexmedetomidine has been discontinued for a minimum of 36 hours (48 hours for lorazepam and midazolam); (d) expected mechanical ventilation days ≥5 days; (e) patients are clinically and biologically stable and pass the weaning screening and are therefore ready to be weaned from mechanical ventilation.

Exclusion criteria are: (a) pregnant or breast-feeding women; (b) preadmission treatment of sleep disturbances; (c) a history of convulsions, psychiatric or neurological disease, sleep apnoea, deafness or blindness; (d) alcohol consumption ≥50 units per week or drug use; (e) liver insufficiency (child-Pugh class C); (f) renal insufficiency (requires dialysis); (g) severe heart failure (the New York Heart Association classification III/IV); (h) intestinal obstruction, ileus, gastroparesis or other conditions likely to affect the enteral absorption of melatonin; (i) the use of drugs that might alter melatonin secretion and decrease plasma levels of melatonin, such as benzodiazepines, NSAIDs, corticosteroids, beta-blockers, haloperidol and amiodarone
[42, 43]; (j) known allergy to melatonin; (k) readmitted to the ICU after randomization to the study; (l) enrolled in another trial.

### Ethical aspects and informed consent

When a patient is identified as eligible for the study, immediate contact will be made with the 24-hour on-call study coordinator who will confirm eligibility. The attending physician will introduce the patient and their family to the study coordinator. The physician will make sure the patient and family know the credentials of the study coordinator and will explain that this person is going to discuss the study program that is being conducted and that this person is qualified to do so. Every relevant aspect of the project will be described. The study coordinator will stop frequently, ask if there are any questions, and request that the family repeat back in their own words what is being discussed to ensure understanding.

The study coordinator will explain that there is a possibility that the patient may suffer from poor sleep quality, and if so, the patient’s health could decline. The coordinator will say that there is a physiological sleep aid that provides good sleep quality without respiratory depression, while facilitating the patient’s condition. Additionally, he will explain that in a small percentage of patients, melatonin could cause headache, dizziness, nausea and drowsiness. The potential advantages of using or not using melatonin will be described. The study coordinator will be especially careful to assure the family that they are free to decline consent without consequences and that they can withdraw consent at any time without impact on treatment. Family members will be provided with contact information for the study coordinator, the local co-investigator and the local ethical committee. Written consent will be obtained in the presence of a witness. A register is kept of all patients evaluated for inclusion and of patients who withdraw from the study. The latter are clinically followed up without their data being analysed in the study.

The study protocol and consent forms were approved by the Institutional Review Board of Fuxing Hospital affiliated with Capital Medical University (approval number KY2014-22) and by the Chinese Clinical Trial Registry (approval number ChiCTR-TRC-14004319). The Fuxing Hospital’s Institutional Review Board gave positive advice for the addition of their ICU as the study site.

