## Abstract

**Background:**

Sleep deprivation is common in critically ill patients in intensive care units (ICU). It can result in delirium, difficulty weaning, repeated nosocomial infections, prolonged ICU length of stay and increased ICU mortality. Melatonin, a physiological sleep regulator, is well known to benefit sleep quality in certain people, but evidence for the effectiveness in ICU sleep disturbance is limited.

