[31]. Most importantly, although melatonin has hypnotic, sedative and analgesic properties, it has few respiratory and hemodynamic effects.

The interest in melatonin as a potential therapeutic or prophylactic agent in the management of sleep disturbance in the ICU derives from the demonstrated low plasma concentrations and altered secretion patterns of melatonin in critically ill patients. Shilo *et al*. studied the day secretions of melatonin in a group of ICU patients compared to a group of patients in ordinary medical wards. They found that the nocturnal peak of melatonin was missing in most ICU patients
[32]. Mundigler *et al*. described a disturbed pattern of circadian secretion of melatonin in ICU patients with sepsis (16 out of 17 patients) but a preserved circadian rhythm in ICU patients who did not have sepsis (six out of seven patients)
[33]. Olofsson *et al*. found that the circadian rhythm of melatonin secretion was abolished in mechanically ventilated patients in the ICU
[34]. Perras *et al*. suggested that the nocturnal melatonin concentrations in ICU patients were negatively correlated with illness severity
[19]. In addition, various drugs commonly used in the ICU have been reported to alter melatonin secretion and to decrease the plasma levels of melatonin
[35] including benzodiazepines, non-steroidal anti-inflammatory drugs (NSAIDs), corticosteroids and beta-blockers. Therefore, low melatonin levels, poor sleep quality and illness have a reciprocal causation interaction and form a vicious circle. The supplementation of exogenous melatonin to remodel the melatonin level in the human body that approaches the physiological state might be one of most effective strategies for improving sleep.

Both melatonin and cortisol are biological markers of the circadian rhythm. Some previous studies have shown that there is a hypo-secretion of melatonin and an overall high cortisol excretion in most patients in the ICU. Cortisol is an important stress hormone that would be invoked by the noise, light and other stressors in the ICU and leads to anxiety and sleep disturbance. It is known that melatonin can reduce the adrenocortical response to stress and down-regulate the synthesis and release of cortisol. Moreover, in addition to reducing the stress, the role of melatonin as an antioxidant and anti-inflammatory agent or part of sepsis treatment is widely discussed. Thus, administration of melatonin might significantly benefit ICU patients.

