Recently, Mistraletti *et al*. studied the pharmacokinetics of melatonin given orally to ICU patients and found a good oral bioavailability of the drug
[36]. Additionally, several studies suggest it can take up to three days to achieve the desired effect of melatonin on sleep quality
[13, 18, 30, 37]. Until now, there have been only three studies investigating the influence of melatonin treatment on sleep quality in critically ill patients. Shilo *et al*.
[37] and Bourne *et al*.
[18] found that melatonin improved sleep quality and sleep length in critically ill patients in the ICU, however Ibrahim *et al*.
[30] found a negative result in their study. There are some inconsistencies regarding the inclusion criteria, the drug included, the sound and light control and the monitoring method in these three studies, specifically as follows:(1) Ibrahim *et al*.’s study included patients who had unlimited use of sedatives and analgesics that might affect serum melatonin levels; (2) there was no uniformity for the control of patient exposure to noise and light among the three studies, which may have a more powerful effect on observed sleep than even the pharmacological levels of melatonin achieved; and, most significantly, (3) they did not use the PSG (the gold standard for assessing sleep) to evaluate sleep quality and ignored the importance of monitoring the all-day sleep, likely because it is very difficult to perform 24-hour PSG in severely ill patients in the ICU.

The aim of the present work is to evaluate the efficacy and safety of melatonin for ICU sleep deprivation. Our hypothesis is that melatonin will improve the sleep quality in ICU patients. The present article proposes a protocol for a clinical study consisting of a double-blind, randomized, placebo-controlled trial with melatonin in adult critically ill patients with ICU sleep deprivation. The present report will follow the guidelines expressed by the Consolidated Standards of Reporting Trials (CONSORT).

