Side effects	Headache, dizziness, nausea, and drowsiness, determined daily by physical examination by the intensivist, and withdrawal symptoms upon discontinuation evaluated after the drugs are stopped.

NREM, None rapid eye movement; SWS, Slow wave sleep; REM, Rapid eye movement; PSG, Polysomnography; RCSQ, Richards Campbell sleep questionnaire; VAS-A, Visual analogue scale-anxiety; CAM-ICU, The confusion assessment method for the intensive care unit.

The primary outcome will be to determine the effect of melatonin administration on the 24-hour sleep-wake cycle and subjective sleep quality, including night/day sleep time, total sleep time(TST), percentages of NREM stage 1/2, slow wave sleep(SWS) and REM, the incidence of arousals per hour, the duration of sleep without waking and the number of sleep periods.

The secondary outcomes will be: (a) objective sleep quality as assessed by the Richards Campbell Sleep Questionnaire (RCSQ); (b) anxiety levels measured using the Visual Analogue Scale-Anxiety (VAS-A); (c) stress levels via measuring the plasma melatonin, cortisone and norepinephrine; (d) levels of oxidative stress; (e) levels of inflammation; (f) the number of delirium-free days in 8 and 28 days; (g) the number of ventilator-free days in 28 days; (h) the number of antibiotic-free days in 8 and 28 days; (i) ICU length of stay; (j) overall ICU mortality at 28 days; (k) the incidence and severity of melatonin side effects in ICU patients.

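### The consent talk presents melatonin's benefit and respiratory safety as established, although the protocol treats efficacy as unproven and claims only few respiratory effects

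*Protocol article*

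**What the plan says.** The protocol article, under Ethical aspects and informed consent, sets out what the coordinator tells the patient and family. After a warning that poor sleep could worsen the patient's health, the coordinator is to say that "there is a physiological sleep aid that provides good sleep quality without respiratory depression", and that it helps the patient's condition. The drug is then named through its side effects: "in a small percentage of patients, melatonin could cause headache, dizziness, nausea and drowsiness". The section also requires that "The potential advantages of using or not using melatonin will be described", together with checks of understanding, freedom to decline or withdraw, and witnessed written consent.

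Other sections are more cautious. The Abstract says that "evidence for the effectiveness in ICU sleep disturbance is limited". The Background counts three studies of melatonin and sleep in critically ill patients: two found a benefit, and the third "found a negative result in their study". It then gives improved sleep as the trial's hypothesis. On breathing and circulation it says that "it has few respiratory and hemodynamic effects". The Discussion accepts that the result may be neutral, in which case more work on safety and efficacy would be needed.

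**The concern.** The sentence prescribed for the coordinator carries three assertions: the drug gives good sleep, it does not depress respiration, and it helps the patient's condition. None is hedged. The first is the question the trial is run to answer. The second goes beyond the protocol's own statement, and the people hearing it have had acute respiratory failure and are about to be weaned from the ventilator. The third turns a hope expressed in the Background into a fact.

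Two things are at stake. The first is whether patients and families consent on accurate information. The second is the self-rated data: the RCSQ and the VAS-A are completed by patients who have already been told that the drug works.

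**Working it through.** The plan gives no figure on this point, so the check is mainly a comparison of texts.

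**Step 1: the assertions against the rest of the article**

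| Told at consent | Stated elsewhere |
|---|---|
| Gives good sleep | Abstract: ICU evidence limited. Background: two positive studies and one negative, none using polysomnography; efficacy is the hypothesis. Discussion: a neutral result is possible. |
| No respiratory depression | Background: few respiratory effects. |
| Helps the patient's condition | Background: administration might benefit ICU patients; this is not given as shown. |

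The first row is a direct conflict. The second is a difference of strength, few against none. The third replaces a possibility with an assertion.

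**Step 2: does the rest of the consent section repair it?** Naming side effects, describing advantages of either choice and assuring freedom to refuse are all proper. None of them says that efficacy is unknown, so the assertion stands.

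**Step 3: which outcomes could be affected?** Under Data collection and management, the RCSQ and VAS-A are self-rated at 9:00 am on day 2 (baseline, before the first dose that evening) and at 9:00 am on day 6. Both ratings follow the consent talk. The Abstract makes polysomnography the primary outcome and the RCSQ secondary.

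**Step 4: effect on the comparison.** Let c be the shift in a rating caused by expectancy common to all patients, and d the drug effect. If the two simply add, the difference between arms is (d + c) − c = d, so the contrast is unchanged. It shrinks only if expectancy takes up part of the room for improvement on the 100 mm scale or overlaps with the drug effect. The documents give no value for this.

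For a difference created by belief alone, let pM and pP be the shares in the melatonin and placebo arms who believe they receive melatonin, and E the shift in mm that this belief causes. Then bias = (pM − pP) × E. All values below are assumptions, with E = 5, 10 and 15 mm:

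- pM = pP = 0.5, or pM = pP = 0.8: 0 mm for every E.
- 0.6 against 0.4: 0.2 × E = 1, 2 and 3 mm.
- 0.7 against 0.3: 0.4 × E = 2, 4 and 6 mm.

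The bias is zero unless belief differs by arm, however strong the common expectancy.

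**The case against.** The strongest reply is that the design already protects the comparison. Every patient hears the same talk before randomisation, the placebo is matched and given in the same way, and patients and all study personnel except the pharmacist are blinded. Expectancy is therefore equal across arms by design. This stands.

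A reader might infer that patients will work out their arm from how they slept or whether they felt drowsy, and so create a false difference in the ratings. The document does not support that. If the drug has no effect on sleep, sleep is no clue to allocation. Drowsiness is described as affecting only a small percentage, which could not readily open a gap in belief of 20 to 40 percentage points. The 1 to 6 mm above shows what such a gap would do; it is not an estimate for this trial.

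A reader might also infer that the RCSQ is part of the primary outcome, because the outcomes section describes that outcome as "the effect of melatonin administration on the 24-hour sleep-wake cycle and subjective sleep quality". The measures listed after those words are polysomnographic, however, and the RCSQ is the first secondary outcome, where it is labelled objective. Read with the Abstract, this looks like swapped labels.

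Finally, the article reports the consent talk in indirect speech, the consent form is not shown, and the ethics board approved it. This limits the point to the stated wording: one cannot conclude that consent as a whole was invalid or that placebo allocation went unexplained. It does not remove the conflict, since the sentence is given as what the coordinator will say. It is also fair that few respiratory effects in general does not strictly contradict absence of respiratory depression in particular. The respiratory part is therefore an overstatement, and the efficacy part is the firm contradiction.

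**Conclusion.** The point holds as a defect of consent information. What patients are told about efficacy conflicts with the Abstract, Background and Discussion, and what they are told about breathing is stronger than the Background supports. This conclusion needs no numerical assumption, and it applies to every patient consented with this wording.

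The effect on the data is secondary and cannot be sized from the documents. Raised expectancy in both arms may reduce the contrast in RCSQ and VAS-A, provided that expectancy and drug effect do not simply add. A between-arm bias is not shown. The primary outcome is not self-rated and is much less exposed, so the point does not undermine the main comparison. It is worth correcting because the repair is cheap and accurate consent information matters even if the expectancy effect is small.

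**What to change.** For patients still to be enrolled, replace the sentence with wording that agrees with the rest of the protocol:

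- it is not known whether melatonin improves sleep in ICU patients, and the earlier ICU studies disagree;
- chance decides whether a patient receives melatonin or a matched placebo;
- vital signs, including respiratory rate, are recorded during the study, as the data collection section already provides.

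Remove the three asserted benefits. Keep the disclosure of side effects, including drowsiness. Check the consent form for the same wording and notify the ethics board of the change.

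The cost is an edit and a notification, with possibly a slightly lower consent rate. The Trial status section says that the study began in February 2014 and has passed one interim analysis, so the change cannot alter what patients already enrolled were told before giving their ratings.

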3). They stress the importance of considering all of those factors (that is, organic and metabolic causes, noise and light, anxiety, the presence of invasive tools and pain) that could contribute to agitation, delirium and pain, and should be corrected before administering any neuroactive drug. Analgesics (particularly opiates) must be used only in case of pain (a Verbal Numeric Rating (VNR) score >3 or a Behavioral Pain Scale (BPS) score >6)
[44]. If delirium (CAM-ICU+) and agitation (RASS >0) appears, after correcting the underlying causes, the non-pharmacological protocol will be applied and potential deliriogenic therapies stopped; only after these interventions may physicians prescribe haloperidol or any other antipsychotic drug and remove these participants according to local guidelines. In these cases, the patient will stop taking the study drug but remain in the study and the investigator will perform the end-of-treatment assessments immediately and the end-of-study visit 28 days later. The trial procedures are shown in Figure 
4.

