### End of participation in the study

Patients will leave the study when the following occurs: (a) the patient refuses to participate in the study; (b) an exclusion criterion appears during the course of the intervention; (c) a severe adverse event occurs; (d) the patient’s condition gets worse; (e) ICU discharge or death.

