The subjective sleep quality refers to the subjective feelings of the nightly sleep status of the patients. The baseline nightly sleep perceptive quality (day 1 9:00 pm to day 2 7:00 am) will be evaluated using the RCSQ at 9:00 am on day 2. The RCSQ contains five 100 mm visual analogue scales (VAS): sleep depth, latency, awakenings, time awake and quality of sleep (higher scores indicate better sleep). The RCSQ was pilot tested in a medical ICU and validated with overnight PSG in medical ICU patients. In our study, patients who are unable to write were assisted; the patients used their current communication strategy to indicate where the investigator should mark the VAS.

Anxiety is defined as a state marked by apprehension, agitation, increased motor activity, arousal, and fearful withdrawal. The baseline anxiety levels are assessed on day 2 at 9:00 am via self-report using the 100 mm VAS-A, which is presented to patients with a vertical orientation such as a thermometer. The bottom of the scale is the statement ‘not anxious at all’ and the top is “most anxious ever.” Patients indicate their current level of anxiety in response to ‘How are you feeling today?’. The VAS-A score is the number of millimetres from the bottom edge of the line (not anxious at all) to the patient’s mark. The VAS-A and the Spielberger State Anxiety Inventory are correlated (r = 0.4916 to r = 0.8219), demonstrating concurrent validity.

During the intervention period (days 2 to 5), outcome-related data, such as the objective and subjective sleep quality, and the anxiety level should be recorded. Analyses are limited to the fourth day (day 5 at 9:00 pm to day 6 at 9:00 am) because the potential chronophypnotic benefits of melatonin are not immediate and may take at least three days to be realised. Therefore, objective sleep quality should be monitored for one 24-hour period using the PSG from day 5 at 9:00 pm to day 6 at 9:00 pm, and the associated parameters and methods as described in the ‘Methods/Design’ section. Meanwhile, the subjective sleep quality and anxiety levels should be evaluated at 9:00 am on day 6 and the related methods have been previously described. In addition, daily information including the vital signs and lab parameters, the SOFA score, neurological monitoring (RASS, CAM-ICU, and GCS), as well as the mode, parameter and duration of mechanical ventilation should be recorded.

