### Statistical analysis

All analyses will be performed according to the intention-to-treat principle, that is, all randomized patients will be analysed in the groups to which they were originally allocated and will be blinded to treatment assignment. Baseline patient characteristics will be compared and described using the appropriate statistics. Categorical variables will be presented as the numbers and percentages and will be analyzed by the *χ*^2^- tests or Fisher’s exact tests, or when appropriate, as relative risks. Continuous variables will be checked for normal distribution by the Kolmogorov-Smirnov test. Normally distributed variables will be expressed by their mean and standard deviation; non-normally distributed variables will be expressed by their medians and 95% confidence levels. Comparisons of continuous variables will be performed using Student’s *t*-test for normally distributed variables and the Mann-Whitney U test for non-normally distributed variables. Appropriate (linear, logistic, or Poisson) regression will be generated for the identification of the determinants of outcomes and for the correction of baseline covariates.

One-way repeated measures analysis of variance (ANOVA) were used to determine differences in the sleep variables, the subjective sleep quality, anxiety levels and plasma levels of melatonin, cortisol and norepinephrine. Twenty-eight day mortality will be analysed according to the Kaplan-Meier method and the results will be compared with the log-rank test hazard ratios and reported with 95% confidence limits. The number of delirium-free days, ventilation-free days and antibiotics-free days will be tested by Student’s *t*-test for normally distributed data and the Mann-Whitney U-test for non-normally distributed data. The differences in adverse events between the intervention and placebo groups are used for safety analyses. All tests of significance will be at the 5% significance level and two-sided. All of the data in this trial will be assessed with SPSS Statistics version 20.0 (SPSS, Chicago, Illinois, United States). The main analysis will be fully specified before unmasking.

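### Intention-to-treat on all randomised patients is promised, but withdrawn patients are barred from analysis, and the rules on removal and leaving the study conflict

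*Protocol article*

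**What the plan says.** All references are to the protocol article.

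- **Statistical analysis:** the intention-to-treat principle governs all analyses, so "all randomized patients will be analysed in the groups to which they were originally allocated".
- **Ethical aspects and informed consent:** a register lists patients screened and patients who withdraw. Of those who withdraw it says: "The latter are clinically followed up without their data being analysed in the study".
- **Trial interventions:** if delirium and agitation lead to an antipsychotic, physicians may prescribe it and "remove these participants according to local guidelines". The next sentence says that in these cases "the patient will stop taking the study drug but remain in the study and the investigator will perform the end-of-treatment assessments immediately", with an end-of-study visit 28 days later. A need for analgesia or sedation stops the study treatment; nothing is said there about leaving the study.
- **End of participation in the study:** patients leave for refusal, if "an exclusion criterion appears during the course of the intervention; (c) a severe adverse event occurs", if their condition worsens, and, as the last item, "e) ICU discharge or death".
- **Study setting and population:** exclusion criterion (i) covers drugs thought to lower melatonin and names haloperidol and benzodiazepines among them.
- **Data collection and management:** "Analyses are limited to the fourth day" of treatment, with polysomnography (PSG) from the evening of day 5 to the evening of day 6, and the sleep questionnaire (RCSQ) and anxiety scale (VAS-A) on the morning of day 6.
- **Table 1:** delirium-free and antibiotic-free days are counted to days 8 and 28, ventilator-free days and mortality to day 28. Delirium is still scored after a delirious patient is discharged from the ICU.

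**The concern.** The analysed population should follow from randomisation alone. Here one sentence includes every randomised patient and another excludes those who withdraw, so the main analysis cannot be carried out as written.

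The exit rules matter because the events behind them are not remote from treatment. The Background section cites evidence that melatonin helps prevent postoperative delirium and may reduce opioid use. Delirium-free days, mortality and side effects are also listed outcomes. If outcome collection stops when a patient worsens or needs an antipsychotic, data could be lost at different rates in the two arms, for reasons linked to outcome. The text does not settle whether collection stops.

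**Working it through.** **Step 1. A randomised patient who withdraws on day 4.** The Statistical analysis section requires this patient to be analysed in the allocated arm. The consent section bars it. The bar carries no condition about consent to data use, so it also reaches data already collected, such as the baseline PSG and any side effects recorded by then. No reading satisfies both sentences.

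**Step 2. A patient given haloperidol on day 4 for delirium with agitation.** Three statements apply:

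- Trial interventions, one sentence: the participant is removed.
- Trial interventions, next sentence: the study drug stops and the patient stays in, with a visit 28 days later.
- End of participation, item (b), with exclusion criterion (i): the patient leaves the study.

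The second contradicts the third outright. It can be squared with the first only if removal means removal from study drug, which is not stated. It is also undefined whether leaving under item (b) counts as withdrawing in the sense of the consent section.

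**Step 3. Exit list against outcomes.** Discharge from the ICU is an exit event, yet Table 1 scores delirium after discharge and counts days to 28. Worsening and severe adverse events are exit events, yet mortality and side effects are outcomes. The list says nothing about whether collection continues.

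**Step 4. The plan's own figures.** Inputs: difference 0.7 h, SD 1.8 h, power 0.8, two-sided alpha 0.05, 82 per group, 20% dropout, 99 per group recruited.

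- n = 2(z₁₋α/₂ + z₀.₈)² × SD²/difference² = 2 × (1.960 + 0.842)² × 3.24/0.49 ≈ 104 per group. The stated 82 is what the one-sided value 1.645 gives.
- 82 × 1.2 = 98.4, rounded up to 99, is the stated figure; 82/0.8 = 102.5 would give 103.

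These mismatches are a separate matter, and this point does not depend on them. The scale of loss that the plan expects is 20% of 198, about 40 patients. With 99 × 0.8 ≈ 79 per arm analysed, two-sided power for 0.7 h is about 69%, against 78% with all 99. The documents do not say how much of the 20% is withdrawal, so this gap cannot be put down to the consent sentence alone.

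**Step 5. Illustration of bias (assumed inputs, none from the documents).** Suppose there is no true effect, a share p of each arm is lost from analysis, and those lost sleep g hours less than those kept. The mean among those kept exceeds the arm mean by p × g, so the bias (melatonin minus placebo) is (p_mel − p_plac) × g.

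| Lost, melatonin | Lost, placebo | g (h) | Bias (h) | Share of 0.7 h |
|---|---|---|---|---|
| 20% | 20% | 0.5–1.5 | 0 | 0% |
| 10% | 20% | 0.5–1.5 | −0.05 to −0.15 | 7–21% |
| 15% | 25% | 0.5–1.5 | −0.05 to −0.15 | 7–21% |
| 10% | 30% | 0.5–1.5 | −0.10 to −0.30 | 14–43% |

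With SD 1.8 h, the nominal 5% test then rejects in about 5% to 18% of trials. Exchanging the arms' loss rates reverses the sign.

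**The case against.** The case for leaving the text alone has four parts.

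1. **The bar on analysis is narrow.** It stands in the consent section, shortly after the right to withdraw, and most naturally means withdrawal by patient or family. This stands. A reader might infer that patients stopped for delirium, worsening or adverse events are also left out of the analysis; the sentence does not say so. The consent form is not shown, so what it permits after withdrawal cannot be checked.
2. **Leaving the study is not exclusion from analysis.** A reader might infer from the exit list that leavers are dropped, giving a selected comparison for mortality, delirium and safety. The documents do not support that. Discharge and death are on the same list, and every patient eventually meets one of them, yet ICU stay and 28-day mortality are analysed. What remains is the silence on whether outcome collection continues.
3. **The two antipsychotic sentences can be read together,** with removal meaning removal from study drug. That is plausible, but it still collides with item (b) and exclusion criterion (i).
4. **The immediate assessments may be harmless.** A reader might infer that patients who stop early contribute a sleep recording from another night to the primary analysis. The text does not say that these assessments include PSG or replace the day 5–6 recording. It also does not say that the day 5–6 recording is still made.

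None of this removes the conflict between the consent section and the Statistical analysis section.

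**Conclusion.** The point holds as a contradiction in the text. The bar on analysing withdrawn patients breaks the stated intention-to-treat rule, and the Trial interventions section conflicts with the exit rule for patients given haloperidol. The exit list leaves follow-up after worsening, severe adverse events and ICU discharge unsettled.

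No size can be put on the consequence from the documents. They give no loss by arm and no sleep figures for patients who leave. It is tempting to claim a definite bias against melatonin, but the range of 0 to 0.30 h rests wholly on assumed rates and deficits. It is zero when loss and deficit are equal in the two arms, and its sign can reverse. The textual conflict depends on none of those assumptions.

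**What to change.** 1. **Consent section.** Replace the sentence so that data collected up to withdrawal are analysed in the randomised arm and follow-up continues, unless consent to data use or to follow-up is itself withdrawn. Check the wording against the consent form.
2. **Reconcile the four sections** (consent, Trial interventions, End of participation, Statistical analysis) by defining three separate states: study drug stopped, follow-up ended, and consent to data use withdrawn. Say which state each listed event leads to and whether day-28 outcomes are still collected. This need not change which clinical events stop treatment, and no such change is proposed.
3. **Sleep assessments.** State that the day 5–6 PSG, RCSQ and VAS-A are still obtained where feasible after drug stop, and that early end-of-treatment assessments do not replace them in the primary analysis.

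The cost is an amendment of wording, plus recordings already planned for every patient. There is a small downside. Some recordings will be made under other drugs. Others cannot be obtained and are then treated as missing: the Background section itself calls 24-hour PSG very difficult in severely ill patients, and the two scales rely on self-report. The change should be made before unmasking, by which point the protocol promises a fully specified main analysis.
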